### The CAVA device

The CAVA system will eventually consist of two separate elements: Hardware and software. The software will be developed from the data collected from this trial and is not fully developed or under test in this trial.

The hardware is composed of two parts. First, there is a reusable device that sits over the ear and records eye and head movements; this is comprised of a logging module containing a battery, microcontroller, accelerometer, data storage facility, an event marker button and connection ports. Second, there are two single-use sensory arrays (electrodes) that adhere to the participant’s face (figure 1).The software will consist of a computer algorithm which will compute head and eye data recorded during a 30-day period. The data used to undertake this work will be uploaded onto a computer from an SD card stored in the device. This data analysis is performed ‘off-line’ after the participant has worn the device.

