Previous approaches to record vertigo attacks include: (1) Wolf described a portable device for recording two channels of eye movement to a floppy disk for 10 minutes.^14^ This system did not allow for continuous monitoring and is now technologically obsolete. (2) Rauch proposed an ambulatory device for recording physiological parameters including ECG, respiration rate, skin temperature, head and eye movement.^15^—this device is no longer in development. (3) Young used video cameras mounted in swimming goggles to record the eyes but patients close their eyes during attacks and attacks can start during sleep.^16^ Wolf’s and Young’s systems are applied at the onset of vertigo which is challenging for attacks that begin without warning. The CAVA system overcomes these limitations and has been proven to be effective in previous research.

During our most recent clinical investigation (NCT04026516), the device recorded the first-ever full example of an acute attack of MD revealing a novel period of nystagmus preceding a full attack.^17^ The data from the CAVA device has allowed a greater insight into the symptoms reported by individuals with an otherwise identical history.^18^ We have also confirmed that a variety of nystagmus signals exhibiting different characteristics can be identified reliably from the data recorded for which we developed novel artificial intelligence (AI) techniques.^12 17 19^

We have completed proof-of-concept work showing that the CAVA system provides information to allow our target diseases to be differentiated by way of five parameters: Nystagmus duration, whether the nystagmus changes direction, the slow phase velocities (speed of the drifting motion), the nystagmus slow phase duration and whether the nystagmus is motion-provoked.^20^ These findings are supported by Young *et al*.^16^ The next step is to demonstrate the consistency of these findings among a larger group of patients to develop algorithms to automatically discriminate these conditions and to determine their diagnostic accuracy.

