## Methods and analysis

### Trial design

This is a single-arm, non-randomised multicentre diagnostic accuracy study using a medical device including an assessment of health economics and the formation of a commercialisation plan.

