### Intervention

All participants fulfilling the eligibility criteria and providing consent will wear the CAVA device for up to 30 days. To balance the consequences of delaying BPPV treatment with not being able to identify the nystagmus associated with BPPV, individuals with BPPV will be offered a particle positioning manoeuvre after 4 days of wear. The CAVA algorithm will then diagnose each patient based only on the data recorded from the device. The accuracy of the system will be tested by comparing the CAVA system’s diagnosis with each patient’s known diagnosis. The results of the algorithm work (‘the diagnosis’) will not be available until the end of the trial and will not be made available to clinicians or patients during the trial.

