### Outcomes

#### Primary outcome

The primary outcome will be nystagmus identification using the algorithm. This will be derived for each participant by comparing the actual nystagmus data and the device-derived nystagmus data. Data will be collated to calculate an overall value for sensitivity and specificity for all participants.

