### Sample size

A minimum sample size of 85 participants for each of the three conditions is required to demonstrate a minimum diagnostic sensitivity of 95% and a specificity of 95% with a 3% margin of error for each condition.

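### The protocol says the software is not under test, yet tests its diagnostic accuracy and sizes the trial to demonstrate a 95% minimum; the design supports only an internally validated, development-stage estimate

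*Protocol article*

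**What the plan says.** All references are to the protocol article; the statistical analysis plan is not shown.

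- **The CAVA device** divides the system into hardware and software. It says what the software is: "The software will consist of a computer algorithm which will compute head and eye data recorded during a 30-day period". Of its status it says: "The software will be developed from the data collected from this trial and is not fully developed or under test in this trial".
- **Intervention** has the algorithm diagnose each patient from the device data, and continues: "The accuracy of the system will be tested by comparing the CAVA system’s diagnosis with each patient’s known diagnosis".
- **Trial design** calls the trial a "single-arm, non-randomised multicentre diagnostic accuracy study using a medical device". The **Introduction** gives the next step as "to develop algorithms to automatically discriminate these conditions and to determine their diagnostic accuracy".
- **Sample size** says that a minimum of 85 participants per condition "is required to demonstrate a minimum diagnostic sensitivity of 95% and a specificity of 95" per cent, and attaches a 3% margin of error for each condition. It states no confidence level, null value or success rule.
- **Data analysis** builds the classifier on all subjects but one, tests it on the subject left out, repeats this for every subject and averages the error. No separate test set is described.

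**The concern.** The hardware records signals, and the diagnosis comes from the software. If the software is not under test, the trial has no diagnostic accuracy to demonstrate. If its accuracy is tested, the statement in The CAVA device is wrong as written.

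What is at stake is the conclusion the trial may draw. Following The CAVA device, the result is an estimate made while the algorithm is being developed. Following Sample size, it is a demonstration that a diagnostic system reaches a 95% floor for each condition. Objective 3 is deployment in the NHS, so the strength of that claim matters to readers outside the trial team. The current text leaves room for the stronger claim about software that the same article says was not tested.

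**Working it through.** **Step 1. Set the statements side by side.**

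| Section | Status given to the algorithm |
|---|---|
| The CAVA device | Developed from this trial's data; not fully developed; not under test |
| Intervention | Its diagnosis is compared with the known diagnosis to test accuracy |
| Introduction | To be developed, and its diagnostic accuracy determined |
| Data analysis | Built and tested on the same participants by leave-one-subject-out cross-validation |
| Sample size | At least 95% sensitivity and 95% specificity to be demonstrated, 3% margin |

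The CAVA device itself identifies the software with the algorithm, so the first two rows conflict directly. The middle rows describe development with internal validation. The last row goes beyond that.

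**Step 2. Try to reproduce the plan's figure of 85.** Inputs from Sample size: p = 0.95, margin d = 0.03, n = 85 per condition. The confidence level is not given, so several are tried in n = z²p(1−p)/d².

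| Two-sided confidence | z | n needed |
|---|---|---|
| 80% | 1.282 | 87 |
| 90% | 1.645 | 143 |
| 95% | 1.960 | 203 |
| 99% | 2.576 | 351 |

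At 95%: 1.960² × 0.95 × 0.05 / 0.03² = 3.8415 × 0.0475 / 0.0009 = 202.7, rounded up to 203. Only a level near 80% comes close to 85, and the article states no such level.

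**Step 3. Read the sentence as precision.** Half-width at 95% confidence = 1.960 × √(0.95 × 0.05 / n).

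- Sensitivity, n = 85: 1.960 × 0.02364 = 0.046, or ±4.6 points.
- Specificity, if its denominator is the other two conditions together (an assumption), n = 2 × 85 = 170: 1.960 × 0.01672 = 0.033, or ±3.3 points.

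Neither meets 3 points.

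**Step 4. Read the sentence as demonstrating a minimum.** Assume this means a two-sided exact (Clopper-Pearson) 95% lower limit above 95%, for sensitivity with n = 85.

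- 85 of 85 correct: lower limit = 0.025^(1/85) = 0.958.
- 84 of 85 correct: lower limit = 0.936.

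So every participant with the condition must be classified correctly. A one-sided 5% test does not relax this: at a true value of 0.95, P(84 or more) = 0.95^85 + 85 × 0.05 × 0.95^84 = 0.013 + 0.057 = 0.070, which exceeds 0.05.

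Chance of 85 of 85, p^85:

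| True sensitivity | Chance |
|---|---|
| 95% | 1.3% |
| 98% | 18% |
| 99% | 43% |

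For comparison, an observed 81 of 85 (95.3%) has an exact 95% interval from 88.4% to 98.7%.

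**The case against.** The strongest reply is that this is one loose phrase. The CAVA device speaks of what the system will eventually consist of, and later calls CAVA a prototype not currently intended to assist diagnosis. The Intervention section keeps the algorithm's results from clinicians and patients during the trial. Together these allow a plain reading: the hardware is the device under investigation, and the software is built and assessed off-line. The Abstract's first objective, to develop an algorithm, fits that reading, as does the stated aim of finding to what extent the conditions can be told apart. This is plausible, but the article does not say it. It also makes the result a development-stage estimate, which is not what Sample size promises.

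The reply also has force against several stronger readings that a reader might infer:

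- *That the plan requires an exact lower limit above 95%.* It states no such rule. The 3% margin points towards precision, and Step 4 holds only under its stated assumption.
- *That refitting the model for each left-out subject is a defect.* It is not. Cross-validation always does this, and here it is chosen to avoid testing on training data. It limits what the result describes; it does not invalidate it.
- *That the primary outcome adds to the same conflict.* That section says "The primary outcome will be nystagmus identification using the algorithm". Identifying nystagmus is a different accuracy from diagnosing the condition, and the article says nystagmus-detection algorithms already exist. The mismatch with Intervention and Sample size is a separate point.
- *That a demonstrated claim will be made for a finished product.* Nothing in the article says so; the wording merely permits it.

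**Conclusion.** The point stands in limited form. The CAVA device contradicts Intervention on whether the algorithm is tested, and Sample size promises a demonstrated minimum that the design does not support. Neither conclusion depends on a calculation.

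The arithmetic adds that 85 per condition fits neither reading of the sample size sentence at 95% confidence: the margin for sensitivity is about 4.6 points against the stated 3, and a lower limit above 95% would allow no errors in 85. The first figure assumes 95% confidence and a true value of 95%. The second assumes an exact two-sided 95% limit and applies to sensitivity only.

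The documents do not show that the software goes untested or that the validation scheme is unsound. What is wrong is the status given to the result. It should be settled before the analysis plan is final.

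**What to change.** 1. Reconcile **The CAVA device** and **Intervention**. State that the hardware is the device under investigation, and that the diagnostic algorithm is developed and internally validated in this trial. Check this against the approved Clinical Investigation Plan V.3.1, which is not shown. If a locked version is in fact to be tested, say which version and on which data.
2. In **Sample size**, replace demonstrating a minimum with estimating sensitivity and specificity, both anticipated to be 95%. Give the confidence level and the margin that 85 per condition yields: about ±4.6 points for sensitivity at 95% confidence. State the denominator for specificity and its margin, about ±3.3 points if that denominator is 170.
3. In **Intervention** and **Data analysis**, say that the reported accuracy is a development-stage, cross-validated estimate, and that no demonstrated-minimum claim will be made for a finished system.

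The cost is a change of wording in four sections and a less favourable stated claim. No extra participants or data are needed.

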**Figure 1 F1:**
[figure not shown]
A doctor modelling the CAVA device. Consent for publication of this image was received. CAVA, continuous ambulatory vestibular assessment.

The device manufacturer is Wright Design Limited. A series of preliminary prototype devices have been manufactured and tested as part of a preliminary programme of work aimed at developing the overall project to this stage. This work has been completed by the primary research team in collaboration with a design agency (Wright Design Limited). The device is a lightweight, durable, body-worn monitoring device that can be worn day and night. It will be worn on the face and head but will minimally intrude into the patient’s normal lifestyle.

The electrode array comprises two separate electrode mounts containing five adhesive electrodes in total. These semiflexible cables are linked by a detachable connector to the logging unit which rests behind the left ear. The mounts are designed to be replaced by the subject on a daily basis. The electrodes are biocompatible to skin for the required duration of wear, this is in order to maximise user tolerance of wearing the device and to reduce the possibility of skin irritation.

The device also includes an indicator LED which glows either green to indicate normal device operation or otherwise shows a flashing/stationary green/red light pattern. Data captured by the device is stored on an inbuilt SD card. This data is intended to be downloaded and viewed by the trial computing team. Data can be downloaded by way of a USB-B interface. Neither the SD card nor the USB-B interface are accessible to the participant wearing the device, minimising the chance of damage to the device or loss of data.

The device is powered by a single AAA battery lasting a minimum of 18 days which is the maximum duration between hospital visits. Site staff will be trained in changing the battery and this will take place on visit 4 (figure 2). Participants do not need to change the battery or open the device in any way.

**Figure 2 F2:**
[figure not shown]
Participant timeline. PIS, Patient Information Sheet

The device will commence logging once the logging unit has been initialised on a computer by a member of the research team which includes the installation of a battery into the device. The event marker button can be depressed to check the status of the device. If the device is functioning properly and connected to the face, the status LED will glow green. Data captured from the device is stored in a text format with each day stored in a separate date-identifiable file.

The electrodes used with the device are intended to be worn for a 23-hour period and all of the equipment should be removed and stored by the participant until the equipment can be returned to the clinic. Once the device and electrode array have been removed, participants can shower or wash before applying a new electrode array to their face as described in the instructions provided to them. They will repeat this process daily. At the end of 30 days, they will return the device to the clinic. The device will be shipped back to the trial team where experts will download and analyse the data from the device. For downloading, the device will be connected to a computer by USB and will appear as a mass storage device on the computer. Files can then be removed from the device as would be normal for any USB storage device. During this file transfer procedure, the device will be powered by USB rather than the internal battery.

The CAVA device is non-sterile and is designed and manufactured under a trial quality management system developed in line with EN13485.

Preliminary prototype devices have been developed to be able to record the maximal ocular excursions and velocities that are observed in clinical practice. These preliminary prototype devices have consistently, accurately, precisely and reliably identified periods of physiological nystagmus in subjects both stationary and in motion and have produced consistent signals at the beginning and end of each trial period.

CAVA is a class 1 medical device worn externally for the purpose of recording data relating to a non-vital physiological process. As such, CAVA poses extremely low levels of risk to participant safety and no risk is posed in the event of failure of the device’s primary function. Device malfunctions will be reported as part of normal trial processes and will only be subject to expedited reporting if the malfunction could have led to an adverse event.

CAVA is currently a prototype device and is not currently intended to assist with clinical diagnoses or treatment. Although the overall function of the device will not change, its appearance as depicted in this document may be subject to minor alterations throughout the device’s development.

### Outcomes

#### Primary outcome

The primary outcome will be nystagmus identification using the algorithm. This will be derived for each participant by comparing the actual nystagmus data and the device-derived nystagmus data. Data will be collated to calculate an overall value for sensitivity and specificity for all participants.

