### Aims and objectives

We will develop the CAVA system’s capabilities from detecting nystagmus to diagnosis based on the novel, long-term data it records. This work is supported by our proof-of-concept data showing that our objectives are feasible. We will demonstrate the potential economic and patient benefits offered by the device and instigate a plan to deploy the system into the National Health Service (NHS).

Aim: Establish to what extent the data from the CAVA system can be used to differentiate three of the most common inner-ear causes of dizziness.

Primary Objective: Enable the CAVA system to differentiate between MD, VM and BPPV.

Objective 2: Quantify the health and economic benefits of an alternative diagnostic pathway involving the CAVA system.

Objective 3: Finalise and instigate a project-exit plan to deploy the CAVA system into general clinical use in the UK publicly funded healthcare systems, the NHS and internationally.

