### Data analysis

The device data will be downloaded by the investigator and securely backed up locally as well as uploaded to the University of East Anglia’s secure research storage for permanent (tape backup) storage. The software will be used to convert the data from its encoded form on the SD card into the waveform samples provided by the device. The signals will then be resegmented into files, each file containing a full calendar day.

To train the algorithms, we require a collection of nystagmus waveform segments collected from a patient each labelled with the underlying diagnosis of the patient’s condition. The nystagmus waveforms from a patient’s data will be gathered by the computational team in two ways. First, by finding the positions of presses of the event marker in the signal and searching around these points for nystagmus-like signals; second by reading the patient’s diary entries and searching for signals at times when they have noted spells of dizziness (of course, these two conditions may often co-occur). Signals in these regions will be carefully assessed for possible evidence of nystagmus and any candidate waveforms will be copied and stored. Any relevant comments by the patient will be copied and stored with the accompanying waveforms. We will also use automatic analysis. We have already developed algorithms that can detect nystagmus-like waveforms with high accuracy and these will be used to both verify any waveforms found by the procedure above and to discover any other nystagmus events that the patient was either unaware of or had not marked.

After confirmation of nystagmus waveforms associated with the three target conditions of the study, algorithms will be built and tested to do automatic diagnosis. The most suitable computational technique for this task is machine learning (ML), sometimes known as ‘AI’. When using ML to make classifications, we aim to make maximum use of the available labelled data without falling into the trap of testing on material that is either part of the training set or is correlated with it which could lead to optimistically biased results. Hence the paradigm used here is to train on all the data except for that from a single subject and then test on that subject’s data. This procedure is repeated for each subject in turn and the average error rate and its SD are estimated. This technique is known as cross-validation.

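### The stated primary outcome, pooled nystagmus detection, does not measure the primary objective or the quantity that sets the sample size, which is diagnosis of MD, VM and BPPV

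*Protocol article*

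**What the plan says.** All references are to the protocol article.

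- **Primary outcome.** "The primary outcome will be nystagmus identification using the algorithm". It is derived by "comparing the actual nystagmus data and the device-derived nystagmus data", and then: "Data will be collated to calculate an overall value for sensitivity and specificity for all participants".
- **Secondary outcomes.** Seven items are listed: adverse events, wear compliance, economics, commercialisation, time to first attack, acceptability and device malfunction. None is a measure of diagnostic accuracy.
- **Aims and objectives.** The aim reads "Establish to what extent the data from the CAVA system can be used to differentiate three of the most common inner-ear causes of dizziness". It is followed by "Primary Objective: Enable the CAVA system to differentiate between MD, VM and BPPV".
- **Sample size.** The 85 participants per condition are to show a "minimum diagnostic sensitivity of 95% and a specificity of 95" per cent, with a 3% margin, separately for each condition.
- **Intervention.** The algorithm diagnoses each patient from the device data alone, and that diagnosis is checked against the one already known.
- **Data analysis.** A classifier for the three diseases is trained on all subjects but one and tested on the one left out, in turn. The final reported result is the project's diagnostic success rate. The same section says that accurate algorithms for detecting nystagmus already exist.

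**The concern.** The outcome labelled primary asks whether nystagmus was found. The objective, the sample size and the planned accuracy test ask which of three diseases the patient has. These are different quantities with different reference standards: the first is judged against the actual nystagmus, the second against the enrolment diagnosis.

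The primary outcome determines the headline claim. If the analysis follows the Primary outcome section, the headline describes a capability that the article says is largely in hand, and the new question gets no formal outcome status. If the analysis follows the objective and the sample size, it departs from the published primary outcome. Either way the reader cannot tell in advance which number is the trial's result.

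**Working it through.** **Step 1: set the sections side by side.**

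| Section | Quantity | Reference | Level |
|---|---|---|---|
| Aims and objectives | Differentiation of MD, VM and BPPV | Diagnosis (implied) | Three conditions |
| Sample size | Diagnostic sensitivity and specificity | Diagnosis (implied) | Each condition |
| Intervention | Algorithm diagnosis | Known diagnosis | Each patient |
| Data analysis | Classification error, diagnostic success rate | Patient's diagnosis | Left-out subject |
| Primary outcome | Nystagmus identification | Actual nystagmus | One overall value |
| Secondary outcomes | No diagnostic measure | – | – |

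Four sections agree with one another. The Primary outcome section differs from them in quantity, reference and level, and the secondary list does not fill the gap.

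**Step 2: does a good primary result imply good diagnosis?** It does not. Take the limiting case in which detection is perfect, so that pooled sensitivity and specificity are both 100%. Let the disease label be assigned at random with probability 1/3 each, in three groups of 85.

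- Expected sensitivity for each condition: 1/3, or 85/3 ≈ 28 of 85.
- Expected specificity for each condition: 2/3, or 170 × 2/3 ≈ 113 of the other 170.
- The stated primary outcome is unchanged at 100% and 100%, because the label does not enter it.

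This is a logical bound, not a forecast.

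**Step 3: check what the sample size refers to.** The inputs from the Sample size section are p = 0.95 and margin d = 0.03. The article gives no confidence level, so a range is shown. The formula is n = z² p(1 − p)/d², with p(1 − p) = 0.0475 and d² = 0.0009.

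| Two-sided confidence (assumed) | n for a 3-point margin | Half-width, n = 85 | Half-width, n = 170 |
|---|---|---|---|
| 80% | 87 | 3.0 points | 2.1 points |
| 90% | 143 | 3.9 points | 2.7 points |
| 95% | 203 | 4.6 points | 3.3 points |
| 99% | 351 | 6.1 points | 4.3 points |

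At 95%, n = 1.96² × 0.0475/0.0009 = 202.7, rounded up to 203, and the half-width with 85 is 1.96 × √(0.0475/85) = 0.046. The stated 85 is not reproduced at 90%, 95% or 99%; only 80% comes close. That is a separate question. What matters here is that the stated basis is diagnostic accuracy within each condition. One pooled proportion over 255 would have a half-width of 1.96 × √(0.0475/255) = 0.027 at 95%, which is not the precision the section describes.

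**The case against.** The strongest reply is that the diagnostic question is not lost. The Intervention section plans the comparison with the known diagnosis, and the Data analysis section plans leave-one-subject-out testing and names the diagnostic success rate as the final result. **This stands.** A reader might infer that the trial will leave its question unanswered, and the documents do not support that. The analysis is planned, but it is missing from both outcome lists.

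It could also be said that The CAVA device section describes the software as not fully developed or under test in this trial, so a detection outcome is the modest choice. But the stated primary outcome itself depends on an algorithm, and the Intervention section does plan to test the diagnostic one.

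Other stronger readings are tempting and should not be drawn:

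- **That the trial could pass on the wrong outcome.** The Primary outcome section sets no success threshold, so one can speak only of a favourable result.
- **That specificity for nystagmus cannot be estimated because everyone analysed has nystagmus.** Recruitment and screening joins its two conditions with and/or, so a participant with data but no qualifying attack may count. Retention gives a recruitment stopping rule, not an analysis set. The primary outcome covers all participants, and the scoring unit is not fixed.
- **That "the average error rate and its SD are estimated" means the spread of individual errors rather than a standard error.** The wording permits either reading.
- **That the harm from MD-versus-VM confusion, or the false-alarm burden, can be given a number.** The introduction describes MD and VM in like terms, as unpredictable attacks lasting hours, but the article gives no misclassification rate or detector specificity from which to calculate one.

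**Conclusion.** The article contradicts itself on what its main result is. The primary outcome is pooled nystagmus identification. The primary objective, the sample size, the accuracy test and the final reported result are all diagnosis of the three conditions, and diagnostic accuracy appears in neither outcome list. This is a wrong primary outcome, not a missing analysis. It is also not something to leave to the statistical analysis plan, since such a plan should analyse the protocol's primary outcome and not replace it.

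The conclusion rests on the text alone. Its size is best put as a possibility: perfect detection is compatible with chance-level classification, one third correct in equal groups. How far the two would diverge in practice cannot be derived from the article. The point should be settled before data lock, because it decides which claim the trial can make.

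**What to change.** By amendment before data lock:

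1. Make the primary outcome the algorithm's diagnosis for each participant, taken from the leave-one-subject-out procedure and compared with the enrolment diagnosis.
2. Report sensitivity and specificity for each condition with 95% confidence intervals, and the full 3x3 table, which shows any confusion between MD and VM directly.
3. Move nystagmus identification to the secondary outcomes.
4. Align the statistical analysis plan, which the article says will be approved before data lock.

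**Cost.** No new data are needed; the device recordings and enrolment diagnoses are already collected. The real downside is timing. Enrolment began in February 2023, and the Data analysis section has diagnosis tests run periodically during the active stage, so diagnostic accuracy may already have been seen when the primary outcome changes. The amendment should therefore be dated and should cite the existing objective and sample-size text as its justification, so that it reads as a correction and not as a choice made on results.

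The amended outcome also exposes the precision available. At an assumed 95% confidence and true values of 95%, the half-widths are about 4.6 points for sensitivity (85 per condition) and 3.3 points for specificity (the other 170), against the 3-point margin stated. The report should give the intervals as they fall.
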